### Recruitment

General Practitioners and psychiatrists practicing in the local area will be mailed recruitment letters and information flyers about the study together with referral forms and an explanation of the project eligibility criteria all of which are approved by the Monash University Human Research Ethics Committee. Referring medical practitioners are requested to provide a K10 score for each potential participant to determine eligibility as part of their referral.

Mail-outs to medical practices will be repeated to maintain the flow of participants to meet the required numbers. Applicants are subsequently screened at initial face-to-face or telephone interview by the researcher. Participants are then provided with an explanatory statement describing the project and after reading it through, those who wish to participate in the study are invited to sign the consent to participate form.

### Randomization

All subjects will be allocated an identification number and then randomly allocated to either the MiCBT group or the control group. Randomization is stratified based on the K10 scores (Levels of psychological distress: mild and moderate K10 score < 30; severe, K10 score ≥ 30), antidepressant or mood stabilizer medication (yes/no) and gender. The randomization procedure is conducted using Stata Version 14 SE by a researcher independent from all other aspects of project implementation, including group facilitation and data collection, using random allocation of treatments balanced in blocks. A sequence of treatments (test or control) are randomly permuted in blocks of size 4. Blocks of size 4 were chosen to ensure a balance of treatments in all group sessions, because groups of size 8 could begin as soon as 16 participants are recruited. Allocation is stratified by three stratification variables, each having two values: gender (M/F), antidepressants (Y/N), K10 score (20+/30+). Therefore a randomization schedule is generated for each of the 8 strata: F N 20+; F N 30+; F Y 20+; F Y 30 + M N 20+; M N 30+; M Y 20+; M Y 30+.

### Blindness

With the exception of meditation practice data, which is collected as described, all other assessments are conducted online, thus minimizing the possibility of researcher bias. Analysis of results will not be blinded.

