### Participant timeline

The baseline measure is the K10 administered by the General Medical Practitioner as part of the referral process. The remaining assessments will be administered 1 week prior to the commencement of the program post randomization (see Table 1) in order to fully standardize the assessment time frame across participants and address the considerable and varied delay between recruitment and commencing the program. Administering pre-treatment assessments as close as possible to the start of the intervention is expected to have the advantage of achieving maximum precision and sensitivity to change in the context of fluctuating mental health conditions with only low risk of systematic observer or participant bias which could nevertheless be readily gauged though pre- and post-randomization K10 analysis. Observer bias is unlikely because the assessments are conducted on-line. Participant bias, such as demoralization following allocation to control, is also considered unlikely as all participants will receive the program within a relatively short time frame and participants who express a strong desire to be allocated to MiCBT immediately will be recommended to seek alternative treatments and alternative treatments are recommended for participants who express a strong desire to be allocated to MiCBT immediately.

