### Data management

Results of the assessments will be kept confidential. Participants are allocated a unique identifier to be used when processing and communicating results. Personal details and results will be kept in separate databases and stored in accordance with Australian Psychological Society Ethical Standards and as outlined in the approved ethics application. Any publication of the results will not be published in a manner that would reveal the identity of any participants. The research dataset, de-identified, may be made publicly available.

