### Statistical analysis

Statistical analysis will be conducted using SPSS version 24 statistical software package. The dependent variables are scores on the two primary outcomes (DASS-21 and the K10), the secondary outcomes (SWLS and FS) and the other mediators (EQ, the MSES-R, the MAIA, and the NAS). The expected outcomes are that the MiCBT group will show significantly changed scores as compared to the wait-list control group, with lower scores on the DASS-21, the K10 and higher scores on the SWLS, FS, the MSES-R, the MAIA, the EQ, and the NAS.

The differential changes in the MiCBT group compared to the control group is the primary focus of the analysis. Analysis will use mixed-model repeated measures (MMRM), the method recommended for clinical trial data [77]. Evidence for the effectiveness of MiCBT will be demonstrated by a significant two-way interaction demonstrating greater change in the outcome measures in the MiCBT group from the control group pre to post intervention. Baseline to follow-up interactions for the MiCBT group will also be examined and changes compared with post intervention data. Results of the trial will be made available to referring clinicians and to participants in the form of a summarized report. Results may be published in journal articles, student thesis and conference presentations.

Intention-to-treat (ITT) analysis will be used because this approach uses all available information. Subjects with incomplete data are not discarded and missing data are not replaced with estimated values. Missing data will be examined and if found to be missing completely at random (MCAR) then the analysis will proceed without replacing missing data with estimated values. If pattern of missingness is not MCAR then multiple imputation will be applied using the strata that defined the non-random missingness.

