This is consistent with the CONSORT standard [78]. If data are non-normal, then it will be analyzed using generalized linear MMRM. The mediational impact of pre to post MAIA, MSES, EQ and NAS will be assessed using the Sobel test, a method for measuring indirect effects [79]. The test assesses the significance of the product of the coefficients for treatment-mediator and mediator-outcome effects. A bootstrapped multivariate extension of the Sobel test will be used to examine both the total indirect effect and the individual effect and the effect of each mediator. The first model will comprise: group (MiCBT vs wait-list control) as the independent variable; clinical DASS-21 and K10 measures as the dependent variables; and MAIA (interoceptive awareness), EQ (metacognitive awareness), MSES-R (Emotion Regulation, Distress Tolerance, Equanimity subscales and total) and NAS (equanimity), scales that reveal significant group x time interactions, as mediators. Two time-frames will be tested for changes over the course of the program itself (mediators measured at 4 weeks; outcomes at 8 weeks) and in the longer term (mediators measured at 8 weeks, outcomes at 6 months). The second model will comprise: group (MiCBT vs wait-list control) as the independent variable: psychological wellbeing SWLS and FS measures (measured at 6 months) as the dependent variables; and MSES-R subscales of Taking Responsibility, Social Skills, Interpersonal Effectiveness and total score (measured at 8 weeks), MAIA (interoceptive awareness), EQ (metacognitive awareness), MSES-R (Emotion Regulation, Distress Tolerance, Equanimity subscales and total) and NAS (equanimity) scales that reveal significant group x time interactions, as mediators.

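### The protocol commits to an unblinded analysis while missing-data and model-family choices stay open until the data are seen; locking those choices on a coded file would be a cheap improvement

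*Protocol article*

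**What the plan says.** The Blindness section says that, apart from meditation practice data, "all other assessments are conducted online, thus minimizing the possibility of researcher bias", and follows this with "Analysis of results will not be blinded". No reason is given for the second statement.

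The Statistical analysis section then describes steps that depend on what the data show:

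- Missing data: "If pattern of missingness is not MCAR then multiple imputation will be applied using the strata that defined the non-random missingness".
- Model family: "If data are non-normal, then it will be analyzed using generalized linear MMRM".
- Mediation models: the candidate scales are restricted to "scales that reveal significant group x time interactions, as mediators".

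Two other sections bear on feasibility. Under Randomization, allocation is carried out "by a researcher independent from all other aspects of project implementation, including group facilitation and data collection". Under Data management, "Participants are allocated a unique identifier to be used when processing and communicating results".

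**The concern.** Participants in a wait-list trial of group therapy cannot be masked, and they rate every outcome themselves. The therapist cannot be masked either. Analysis is a stage at which masking is practicable, and the protocol gives it up explicitly. This is a stated choice, so a separate analysis plan that followed the protocol would also be unblinded.

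An analyst who knows the arms, and who can see the between-arm result under each option, may lean towards the imputation model or outcome distribution that favours MiCBT, even without intending to. That would add an avoidable source of doubt to a trial already resting on unblinded self-report, and a positive result would be harder to defend.

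**Working it through.** No figure in the protocol is in dispute and no arithmetic settles the point. The check sets the sections side by side.

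1. **What the safeguard covers.** Online completion acts when the participant answers: no interviewer can influence the response. Scoring, missing-data assessment and model choice all come later, so the safeguard in the Blindness section does not reach them.

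2. **Which decisions are open.**
   - *Missing data.* The analyst must judge whether missingness is completely at random and, if not, which strata explain it. This decision is likely to arise: the Sample size section allows for 20% attrition, and 0.20 × 120 = 24 of the planned 120 participants.
   - *Model family.* The switch to a generalized linear model depends on finding non-normality. The article gives no test, threshold, distribution or link. Such detail may sit in a separate plan, and its absence is not the point. The point is that the choice depends on the data and the person making it is not masked.
   - *Mediators.* Scales enter according to whether their group-by-time interaction is significant.

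3. **Whether masking would help each one.**
   - *Missing data: yes.* Missingness can be tabulated by stratum and coded arm without looking at any outcome contrast.
   - *Model family: yes.* The shape of the residuals can be judged without reading the treatment effect.
   - *Mediators: no.* Whether an interaction is significant is the same whichever arm is called A, so hiding the labels changes nothing.

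4. **What masking would need in this trial.**
   - *A person to code the arms.* The Randomization section describes a researcher separate from delivery and data collection, who is a natural candidate.
   - *New participant IDs.* The existing ID is used in the emailed survey links and in processing results. Anyone who has worked with those IDs may know which arm they belong to, so relabelling the arms alone could fail.
   - *Removal of arm-revealing items.* According to the Data collection section, programme-evaluation questions at 8 weeks and adherence questions at 6 months go to the MiCBT group only. Practice logs relate to the programme.
   - *A lock before comparison.* An analyst who sees the A-versus-B results under both options can still pick between them. The order of steps therefore matters as much as the labels.

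5. **Size.** The document does not say how far results would differ between the options or who would choose. No magnitude can be derived.

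**The case against.** The strongest reply is that the protocol discloses the lack of blinding openly and contradicts nothing, so asking for a masked analyst is a preference. It can be added that the outcomes are fixed-item scales with little room for judgement in scoring, that masking may fail if group means reveal the arm, and that the Data Availability section promises de-identified data for reanalysis.

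Much of this stands. The point is a weakness and not an inconsistency, and masking would be imperfect. Reanalysis, however, comes after publication and does not show which decisions were taken with knowledge of the arms. Nor does the reply explain why a cheap protection was declined.

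A reader might infer more than the document supports:

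- *That outliers or late questionnaires could be dropped to favour MiCBT.* No section provides for such exclusions. The Statistical analysis section commits to intention to treat and keeps participants with partial data. An effect-size shift built on excluding a few extreme participants therefore has no basis here.
- *That the analyst is the researcher who screens or treats participants.* The PhD setting makes this plausible, but no section says who runs the analysis. Nor does any section say who keeps the allocation list.
- *That the bias can be sized by the type I error from reporting the better of two analyses* (for two independent tests, 1 − 0.95² = 9.75%). An analyst with A/B labels who saw both results could do the same, so this figure does not measure the lack of masking.
- *That "Observer bias is unlikely because the assessments are conducted on-line" is offered as protection for the analysis.* In the Participant timeline section it concerns the pre-treatment assessments only.

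**Conclusion.** The concern holds as a design weakness with an inexpensive remedy. The protocol chooses an unblinded analysis without a reason, leaves the missing-data and model-family decisions to be made on the observed data, and relies on a safeguard that does not protect them. The bias is possible, not demonstrated, and its size and direction cannot be quantified from the document.

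The conclusion rests on two assumptions: that someone independent of delivery and data collection can prepare the coded file, which the Randomization section makes likely but does not assign; and that the open decisions are not already fixed by rule in a plan not shown. If they are, the gain from masking is smaller.

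**What to change.** Replace the sentence in the Blindness section with wording such as:

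> Scoring, missing-data and distributional decisions will be made and recorded on a file with new participant IDs, without meditation logs and MiCBT-only items, and with arms coded A/B by a person independent of delivery and data collection (for example the randomization researcher). These decisions are locked before any between-arm outcome comparison; the primary model is then run on the coded arms before the code is broken.

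The cost is about one additional data file and a short decision record, plus merging the MiCBT-only data afterwards. The remaining limitation is that a large effect may hint at the arm.

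Two matters need separate attention, because this change does not cover them: stating in advance the rules for the imputation and distribution choices, and the selection of mediators by significance.

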### Data collection

In addition to the quantitative measures previously described participants in the MiCBT group will be asked some additional qualitative questions at the end of the 8-week program evaluating the program and asking about any adverse events they may experience with their meditation practices during the MiCBT program. Additionally, at the 6-month follow up, participants in the MiCBT group will be asked questions relating to adherence to meditation practices and any changes to treatment. Participants in the control condition will complete all measures at the same four time points as the treatment group and receive treatment as usual during this time.

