## Methods/design

This study is a randomized controlled trial as it is an early stage trial. Participants will be recruited through medical practitioner referral from the metropolitan region of Melbourne randomized to one of two treatment conditions: MiCBT or a control condition. Both conditions will continue with usual treatment which may include medication and/or ongoing psychological therapy throughout the trial. It was not feasible due to lack of resources to conduct an active control for this study which will be conducted in a private practice setting in the context of a PhD project. However, a wait-list control condition control is appropriate for such an early phase RCT. In addition, the question as to whether any positive treatment outcomes reflect specific or general therapy effects is being addressed to some extent through the mediation analyses.

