#### Adverse effects

There is a weekly check in with participants about their practice and any issues raised are addressed. In the event of participants experiencing difficulties in relation to their meditation practice the following actions may be taken: a) modify the type of practice for the coming week or b) provide some individual counselling to the participant. The 6-month follow-up questionnaire includes a question about the occurrence of any adverse effects or other difficulties thought to be as a result of meditating. The questions were taken from a recent study about the broad ranges of experiences that occur in association with meditation practices [74]. The questions are:
“Did you have any unexpected, challenging, or difficult experiences that you associate with your practice of meditation?”“How did these experiences impact your life”? [74].

All measures will be administered on line using Qualtrics survey software, with the exception of the amount of meditation practice which will be recorded by each participant and reported privately on a personalized form each week. There are inadequate resources available for this PhD study to administer the qualitative questions in person.

Participants are emailed a link to the measures utlizing their unique identification number. Reminder emails are sent to those who do not respond and if there is still no response the participant is telephoned.

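### Treatment changes are asked of the MiCBT arm only, and adverse-experience questions are tied to meditation, so neither can be compared between arms

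*Protocol article*

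**What the plan says.** Under Methods/design, the protocol article leaves other care open in both arms: "Both conditions will continue with usual treatment which may include medication and/or ongoing psychological therapy throughout the trial". Medication is otherwise recorded only as a stratification factor at randomization (Randomization).

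The only question about later treatment is in Data collection, where "at the 6-month follow up, participants in the MiCBT group will be asked questions relating to adherence to meditation practices and any changes to treatment". Controls, according to the same section, complete the study measures at the same four time points and receive usual treatment. None of the instruments described under Measures records concomitant treatment.

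Adverse experiences are covered in three places:

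- At week 8, "participants in the MiCBT group will be asked some additional qualitative questions at the end of the 8-week program", among them one "asking about any adverse events they may experience with their meditation practices during the MiCBT program" (Data collection).
- During the program, "There is a weekly check in with participants about their practice and any issues raised are addressed" (Adverse effects).
- At 6 months, "The 6-month follow-up questionnaire includes a question about the occurrence of any adverse effects or other difficulties thought to be as a result of meditating" (Adverse effects). No arm is named. The lead question is "Did you have any unexpected, challenging, or difficult experiences that you associate with your practice of meditation", and the follow-up question refers back to it.

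Participant timeline adds that "participants who express a strong desire to be allocated to MiCBT immediately will be recommended to seek alternative treatments".

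**The concern.** The comparator is whatever care controls actually receive, and the plan lets that care change during the trial. If controls start other treatment more often than MiCBT participants do, the observed difference is smaller than the effect of adding MiCBT to unchanged care. If MiCBT participants do so more often, it is larger (in both cases assuming the other treatment helps). A reader of the results will want to know which happened. The plan collects that information in one arm, at one late time point.

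The same asymmetry affects safety. A count of difficult experiences in the MiCBT arm is hard to read without a count from comparable people who did not receive the program, because such experiences also occur in distressed patients under usual care.

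An analysis plan cannot repair this afterwards, since data not collected cannot be analysed.

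**Working it through.** The plan states no figure on this point, so the check is to set the sections side by side.

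| Information | MiCBT arm | Control arm | Section |
|---|---|---|---|
| Antidepressant or mood stabilizer | At randomization | At randomization | Randomization |
| Change in treatment afterwards | 6 months | None stated | Data collection |
| Adverse events with meditation, week 8 | Yes | None stated | Data collection |
| Weekly check-in on practice | Yes, in effect | Not applicable | Adverse effects |
| Adverse-effects item, 6 months | Yes | Arm not named; wording presupposes meditation | Adverse effects |
| DASS-21 and K10 | Four time points | Four time points | Primary and secondary outcomes; Data collection |

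**1. Do controls get the treatment-change question by another route?** Data collection has controls complete all measures. However, it introduces the MiCBT group's questions as additional to the quantitative measures already described, and none of those measures covers treatment. As printed, the answer is no. With 120 recruited and equal allocation, that is 120/2 = 60 participants with no stated record of treatment changes.

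**2. Does the timing serve the main contrast?** Statistical analysis bases effectiveness on the group-by-time interaction from before to after the intervention, that is, to week 8. The question comes at 6 months. Its recall period is not given, so it might reach back over the first 8 weeks, but in one arm only.

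**3. Are the 6-month results affected too?** Yes. Aims and hypotheses expects gains to be maintained over six months, and Mediator hypotheses and Statistical analysis use group to predict 6-month outcomes. Treatment changes up to then would be known in one arm.

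**4. What does one-arm information identify?** Let δ be the benefit of adding MiCBT to unchanged usual care, e the average benefit of a newly started treatment, and q_M and q_C the proportions starting one in the MiCBT and control arms. With additive effects (an assumption), the expected observed benefit is

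D = δ + e × (q_M − q_C).

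The plan would give q_M, at 6 months, and not q_C. The difference q_M − q_C is therefore unknown in both size and sign. The documents give no value for e, q_M or q_C, so no numerical shift can be derived from them.

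**5. Can harm be compared?** Symptom worsening can, from DASS-21 and K10 scores in both arms. Other adverse experiences cannot. The week-8 question goes to one arm, and the 6-month question asks about the respondent's own meditation, so even if controls receive it, those who do not meditate have nothing to report.

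**The case against.** The strongest reply is that the trial compares MiCBT added to usual treatment with usual treatment, in a private-practice effectiveness setting. Changes in usual care are then part of the comparator, and randomization protects the contrast whether or not they are recorded. This stands. A reader might infer that neither a positive nor a null result could be attributed to MiCBT, and the documents do not support that. If controls find effective care elsewhere, the difference shrinks, which does not undermine a positive result. What remains is a poorly described comparator and a null result that is hard to interpret.

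Other strong readings are tempting and also fail:

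- **That harm cannot be compared, or that deterioration on the wait list goes unseen.** DASS-21 and K10 are collected in both arms at all four time points.
- **That every adverse-experience question is confined to the MiCBT arm.** This is explicit only for week 8. The 6-month item names no arm. Its weakness as a comparison lies in its wording, although a meditation-specific item is legitimate for the exposed arm.
- **That the advice to seek alternatives sends controls to other treatment.** Participant timeline does not say whether the advice comes before or after allocation. If before, it may divert people from the trial and add no co-intervention. The point does not need it, because Methods/design already leaves other care open.
- **That a definite loss of power can be stated.** Any such figure would rest on assumed uptake and efficacy that the documents do not give.

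Finally, the article is condensed, and the full questionnaire may ask controls more. That is possible. But the article does more than stay silent on treatment changes: it assigns the question to one arm and one time point. If controls are in fact asked, the text should say so.

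**Conclusion.** The point holds in a limited form. As described, treatment changes after randomization are recorded for one arm, at 6 months only, and cannot be compared between arms for the week-8 contrast or the 6-month outcomes. Adverse experiences other than symptom worsening have no usable control reference. The consequence is for interpretation: the comparator cannot be fully described, and a small or null effect cannot be set against what controls received. The randomized comparison itself remains valid.

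No numerical size can be attached. The conclusion assumes that the full questionnaire matches the article's account and that few controls meditate, since they are not taught to within the comparison period. The change is worth making because it is cheap and cannot be made after data collection.

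**What to change.** In the existing online survey, ask both arms the same short items at week 8 and at 6 months:

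- any change in medication or psychological treatment since the last assessment;
- any unexpected difficulty or adverse experience, worded without reference to meditation.

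Keep the meditation-specific item for the MiCBT arm, and state in Adverse effects which arm receives it at 6 months.

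Report both new items descriptively by arm, together with the proportion in each arm that deteriorates on the DASS-21 and on the K10, from scores already collected. Do not add a sensitivity analysis that splits or adjusts by treatment change. That variable arises after randomization and may depend on allocation, so conditioning on it could introduce bias.

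The cost is a few extra survey items, slightly more burden on participants and an ethics notification. No new visits are needed.
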